| **Statistical Considerations**  **& Sample Size** | **Statistical Considerations**  The efficacy will be assessed by estimating the difference between the two treatment arms in the proportion of participants experiencing clinical worsening during their hospital stay.  Safety will be assessed by estimating the difference between the two treatment arms in the proportion of participants who experience at least one bleeding event (major or non-major) during their hospital stay.  Relative risk (RR) will be used as measure of association, which will be reported with its 95% confidence interval.  The differences between the two arms in the variation of:   1. D-dimer level 2. Plasma fibrinogen levels   3) Mean platelet Volume  4) Lymphocyte/Neutrophil ratio  5) IL-6 plasma levels  at 3 time points (at randomization, at 48 hours and 96 hours) will be assessed.  These outcomes will be compared by using their mean values and summary indicators.  Overall survival, survival free from any cardiovascular event, such as Acute Myocardial Infarction [AMI], Objectively confirmed, symptomatic arterial or venous thromboembolism [TE] and survival free from need for either non-invasive or invasive mechanical ventilation will be also estimated. They will be reported by using Kaplan-Maier curves and compared by using hazard ratio (HR).  **Sample size**  300 participants will be needed to detect a relative reduction of 50% of clinical worsening. We hypothesized that the percentage of participants who experience clinical worsening in the LMWH low dose group would be around 25-30% and set an alpha error of 0.05 and beta-error of 0.20. | |
| **Treatment Schedule** | **Control group (Low Dose):** Enoxaparin (Inhixa®) 4000 IU subcutaneously once daily.  **Intervention group (High dose**): Enoxaparin (Inhixa®) 70 IU/kg subcutaneously twice daily.  Participants will receive the dose of Enoxaparin according to the protocol until the occurrence of at least one of the following events:   1. One of the events included in the primary outcome 2. Hospital discharge 3. Any adverse events and clinical condition requiring interruption of the scheduled intervention according to the judgement of the physician in charge | |

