**Duration of follow-up**

Each patient will be followed-up until hospital discharge. Information about the status (dead/alive) of patients who are discharged from hospital before 30 days will be sought on Day 30 from randomisation.

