**2.4.2 Secondary Efficacy Endpoints:**

**Any of the following events occurring within the hospital stay**

1. Death
2. Acute Myocardial Infarction [AMI]
3. Objectively confirmed, symptomatic arterial or venous thromboembolism [TE]
4. Need for either non-invasive - Continuous Positive Airway Pressure (Cpap) or Non-Invasive Ventilation (NIV) - or invasive mechanical ventilation for patients, who are in standard oxygen therapy by delivery interfaces at randomisation
5. Need for invasive mechanical ventilation for patients, who are in non-invasive mechanical ventilation at randomisation
6. Improvement of laboratory parameters of disease severity, including:
   - D-dimer level
   - Plasma fibrinogen levels
   - Mean Platelet Volume
   - Lymphocyte/Neutrophil ratio
   - IL-6 plasma levels

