**2.4.3 Primary safety endpoint:**

Major bleeding, defined as an acute clinically overt bleeding associated with one or more of the following:

- Decrease in haemoglobin of 2 g/dl or more;
- Transfusion of 2 or more units of packed red blood cells;
- Bleeding that occurs in at least one of the following critical sites [intracranial, intraspinal, intraocular (within the corpus of the eye; thus, a conjunctival bleed is not an intraocular bleed), pericardial, intra-articular, intramuscular with compartment syndrome, or retroperitoneal];
- Bleeding that is fatal (defined as a bleeding event that was the primary cause of death or contributed directly to death);
- Bleeding that necessitates surgical intervention

Time to the occurrence of each of these events will be recorded.

Each of these events will be analysed as a binary outcome and as a time-to-event one.

- - 1. **Secondary safety endpoint:**

Clinically Relevant non-major bleeding, defined as an acute clinically overt bleeding that does not meet the criteria for major and consists of:

1. Any bleeding compromising hemodynamics
2. Spontaneous hematoma larger than 25 cm^2^, or 100 cm^2^ if there was a traumatic cause
3. Intramuscular hematoma documented by ultrasonography
4. Epistaxis or gingival bleeding requiring tamponade or other medical intervention
5. Bleeding from venipuncture for >5 minutes
6. Hematuria that was macroscopic and was spontaneous or lasted for more than 24 hours after invasive procedures
7. Hemoptysis, hematemesis or spontaneous rectal bleeding requiring endoscopy or other medical intervention
8. Any other bleeding requiring temporary cessation of a study drug.

Time to the occurrence of each of these events will be recorded.

Each of these events will be analysed as a binary outcome and as a time-to-event one.

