**4.2 Statistical Methods**

All patients enrolled in the study will be entered in the full analysis set independently of his/her treatment time. The intention to treat population will be considered for primary analysis. A descriptive statistical analysis will be carried out to summarise every relevant variable. At baseline, categorical data will be summarised by using counts and percentages, whilst continuous variables will be presented using the number of patients, mean, standard deviation, median, minimum, and maximum. Comparison between binary outcomes will be performed by using Relative Risks (RRs), whereas for continuous data, the difference of means (DMs) will be used. Comparisons involving time to event data will be displayed by using Kaplan-Maier survival curves and summarised by Hazard Ratios (HRs).

All measures of association will be presented with their 95% confidence interval. A result will be considered as statistically significant if its p-values will be less than 0.05 (5%).

The analyses will be performed by using STATA software.

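### Kaplan-Meier is fixed for bleeding and other single non-fatal in-hospital events, so the curves overstate the proportion affected when patients die or are discharged first; the planned relative risks are unaffected

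*Protocol*

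**What the plan says.** Section 4.2 of the protocol gives a single rule for time-to-event outcomes: "Comparisons involving time to event data will be displayed by using Kaplan-Maier survival curves and summarised by Hazard Ratios (HRs". It makes no exception for outcomes that death can prevent.

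The outcomes that fall under this rule are set in section 2.4. For major bleeding, and again for clinically relevant non-major bleeding, the protocol states: "Each of these events will be analysed as a binary outcome and as a time-to-event one". The same sentence closes the secondary efficacy endpoints, which list AMI, thromboembolism and ventilation one by one under the line "Any of the following events occurring within the hospital stay".

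The synopsis describes the Kaplan-Meier outcomes differently: "Overall survival, survival free from any cardiovascular event, such as Acute Myocardial Infarction [AMI" and thromboembolism, and "survival free from need for either non-invasive or invasive mechanical ventilation will be also estimated". Read as event-free survival, these count death as an event. The synopsis names no Kaplan-Meier outcome for bleeding; there it compares proportions by relative risk.

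Two further statements matter. Section 4.2 also says "Comparison between binary outcomes will be performed by using Relative Risks (RRs", so every one of these endpoints has a binary analysis as well. On follow-up: "Each patient will be followed-up until hospital discharge"; after that, only vital status at Day 30 is sought.

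**The concern.** A patient who dies without bleeding cannot bleed later. A Kaplan-Meier curve for bleeding must censor that patient, which treats the death as if it had merely hidden a later bleed. One minus Kaplan-Meier then exceeds the proportion of patients who bleed. Neither bleeding definition counts death as an event, apart from fatal bleeding within major bleeding. AMI, thromboembolism and ventilation have the same problem when analysed as single events.

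Discharge alive raises the same issue. The secondary efficacy events are defined within the hospital stay, and follow-up for all non-fatal events ends at discharge. Censoring at discharge therefore projects in-hospital risk onto people who have left the period in question.

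At stake is how the primary safety endpoint will look. A reader will take the height of a bleeding curve as the risk of bleeding, and it will not match the proportion reported beside the relative risk. This is more than a detail left for a SAP, because the protocol positively names the estimator.

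**Working it through.** **Plan's own figures.** The plan gives no figure for this point. Its sample size reproduces: for 25% versus 12.5%, two-sided 5% and 80% power, the unpooled formula gives 150 per arm, or 300. The argument does not depend on it, but 150 per arm is used below to judge size.

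**Inputs.** Major bleeding 2.7% on high dose (section 2.4.4, risk/benefit). Venous thromboembolism up to about 8% on general wards (section 1.1). Mortality about 30% on low-dose heparin (section 2.4.4), used only as an upper bound. Ventilation risk of 20% is an assumption. The protocol gives no rate of death before the event, so 5% to 30% is assumed. Hazards are taken as constant.

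**Death only.** Let c be the true proportion with the event and d the proportion dying first by the horizon. The total cumulative hazard is H = -ln(1 - c - d), the event's share is h = H x c/(c + d), and one minus Kaplan-Meier is 1 - exp(-h).

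Example, c = 2.7% and d = 15%: H = -ln(0.823) = 0.1948; h = 0.1948 x 0.027/0.177 = 0.0297; 1 - exp(-0.0297) = 2.93%.

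| True proportion | 5% die first | 10% | 15% | 30% |
|---|---|---|---|---|
| 2.7% (major bleeding) | 2.77% | 2.85% | 2.93% | 3.22% |
| 8% (thromboembolism) | 8.2% | 8.4% | 8.7% | 9.6% |
| 20% (ventilation, assumed) | 20.6% | 21.2% | 21.8% | 24.2% |
| Relative overstatement | about 3% | 5-6% | 8-9% | 19-21% |

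**Between arms, death only.** Two scenarios give different pictures.
- Equal proportions bleeding (2.7% in both arms), with 30% dying first on low dose and 15% on high dose: the curves read 3.22% and 2.93%. The hazard ratio is 0.0297/0.0327 = 0.91, while the relative risk is 1.00. With 10% versus 5% dying first, the hazard ratio is 0.97.
- Equal bleeding hazard, with death hazards that alone would give 30% and 15% mortality: Kaplan-Meier reads 2.70% in both arms, while the true proportions are 2.28% and 2.50%. The overstatement is 19% and 8%.

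**Discharge censored as well.** Suppose 95% of patients have had the event, died or been discharged by the horizon. Then H = -ln(0.05) = 2.996. For c = 2.7%, h = 2.996 x 0.027/0.95 = 0.0851, and one minus Kaplan-Meier is 8.2%, about three times the truth. This figure is the same however the remaining 92.3% splits between deaths and discharges.

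**Does treating death alone as competing cure it?** No. With 10% dying first, the death hazard is 2.996 x 0.10/0.95 = 0.3153. Aalen-Johansen with discharge still censored gives (0.0851/0.4005) x (1 - exp(-0.4005)) = 7.0%. With discharge alive also competing, it gives (0.027/0.95) x 0.95 = 2.7%, which agrees with the binary proportion.

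**The case against.** The strongest reply is that no analysis in the protocol takes an absolute risk from these curves. Section 4.2 uses them for display, the proportions come from the binary analysis, and the hazard ratio with deaths censored is a legitimate cause-specific one. That stands. It confines the fault to the curves and to reading the hazard ratio as a comparison of risks.

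The reply continues that the effect is negligible in this trial. With 150 per arm, 2.7% is about 4 bleeds, and one bleed is 0.67 points. The gap between 3.22% and 2.93% is 0.29 points, less than half a patient. A hazard ratio of 0.91 on 4 bleeds per arm has a 95% interval of roughly 0.23 to 3.6 (standard error of the log about 0.71, from the square root of 1/4 + 1/4). That also stands for deaths alone. It does not stand for discharge, where the distortion is about threefold under the stated assumption.

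The 30% setting also sits poorly with section 2.6, which assumes 25-30% in controls for the whole composite, death included. Thromboembolism at 8% plus 30% dying first would already be 38%. Hence 30% is only an upper bound here.

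A reader might go further and infer three things that the documents do not support:
- *That the plan favours high dose on safety.* This follows only if proportions are equal, deaths are fewer on high dose and discharge is ignored. With equal hazards the Kaplan-Meier curves coincide, and once discharge is censored the direction depends on both exits.
- *That the hazard ratio contradicts the relative risk.* They answer different questions and need not agree when deaths differ.
- *That AMI, thromboembolism and ventilation are misanalysed throughout.* Under the synopsis wording, death counts as an event and does not compete.

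**Conclusion.** The point holds for both bleeding endpoints, and for AMI, thromboembolism and ventilation where sections 2.4.2 and 4.2 treat them as single events. For those three the synopsis says something else, and the two texts must be reconciled.

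Death alone has a modest effect: about 3-9% relative at 5-15% dying first and up to about 20% at 30%, or 0.1-0.5 percentage points on a 2.7% bleeding risk. Censoring at discharge is the larger matter. These sizes rest on constant hazards and on assumed death and discharge rates; the protocol gives neither for this trial.

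The relative risks are untouched, and death does not compete with the primary composite, which includes it. This is a correction to how in-hospital event risks, above all the primary safety endpoint, are displayed and labelled. It does not challenge the primary efficacy comparison.

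**What to change.** Change section 4.2 as follows.

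1. Keep Kaplan-Meier for overall survival and for composites that count death as an event.
2. Align section 2.4.2 with the synopsis, stating whether cardiovascular events and ventilation are analysed as event-free survival, as single events, or as both.
3. For each single non-fatal in-hospital endpoint, bleeding above all, replace the Kaplan-Meier curve with the Aalen-Johansen cumulative incidence, with death and discharge alive both as competing events. Naming death alone is not enough, as the 7.0% result shows.
4. Label the hazard ratio for these endpoints as cause-specific, and show the cause-specific hazard ratio for death without the event beside it.

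The cost is wording, plus one more hazard ratio per endpoint. Event times are already to be recorded and patients are followed to discharge, so no new data are needed.

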| **Primary Study Objective(s)** | To assess whether high doses of Low Molecular Weight Heparin (LMWH) (ie. Enoxaparin 70 IU/kg twice daily) compared to standard prophylactic dose (ie, Enoxaparin 4000 IU once day) are:  a) more effective to prevent clinical worsening, defined as the occurrence of at least one of the following events, whichever comes first, during hospital stay:   1. Death 2. Acute Myocardial Infarction [AMI] 3. Objectively confirmed, symptomatic arterial or venous thromboembolism [TE] 4. Need for either non-invasive - Continuous Positive Airway Pressure (Cpap) or Non-Invasive Ventilation (NIV) - or invasive mechanical ventilation for patients who are in standard oxygen therapy by delivery interfaces at randomisation 5. Need for invasive mechanical ventilation for patients who are in non-invasive mechanical ventilation at randomisation 6. Similar in terms of major bleeding risk during hospital stay |  |
| **Secondary Study**  **Objectives** | To assess whether high doses of Low Molecular Weight Heparin (LMWH) (ie. Enoxaparin 70 IU/kg twice daily) compared to standard prophylactic dose (ie, Enoxaparin 4000 IU once day) differ in terms of the following events occurring during hospital stay:   1. Laboratory parameters of disease severity, including: 2. D-dimer level 3. Plasma fibrinogen levels 4. Mean Platelet Volume 5. Lymphocyte/Neutrophil ratio 6. IL-6 plasma levels 7. Clinically relevant non-major bleeding 8. Death during hospital stay and at 30 days 9. Acute Myocardial Infarction [AMI] 10. Objectively confirmed, symptomatic arterial or venous thromboembolism [TE] 11. Need for either non-invasive - Continuous Positive Airway Pressure (Cpap) or Non-Invasive Ventilation (NIV) - or invasive mechanical ventilation for patients, who are in standard oxygen therapy by delivery interfaces at randomisation 12. Need for invasive mechanical ventilation for patients, who are in non-invasive mechanical ventilation at randomisation | |

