**Mortality at 30 days**

Information about patients’ status will be sought in those who are discharged before 30 days on Day 30 from randomisation.

Time to the occurrence of each of these events will be recorded.

Each of these events will be analysed as a binary outcome and as a time-to-event one.

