**2.6 SAMPLE SIZE**

The target sample size is based on the hypothesis that LMWH administered at high doses versus low doses will significantly reduce the risk of clinical worsening. The overall sample size in this study is expected to be 300 with a 1:1 randomisation ratio. Assuming an alpha of 5% (two tailed) and a percentage of patients who experience clinical worsening in the control group being between 25% and 30%, the study will have 80% power to detect at least 50% relative reduction in the risk of death between low and high doses of heparin.

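### Section 4.2 calls any result with p below 0.05 statistically significant, so the 12 secondary endpoints carry the same unadjusted rule as the primary endpoint

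*Protocol*

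**What the plan says.** Protocol section 4.2 (Statistical Methods) closes its account of the analyses with a general decision rule: "A result will be considered as statistically significant if its p-values will be less than 0.05 (5"%). The sentence before it sets the interval convention: "All measures of association will be presented with their 95% confidence interval". Neither sentence names an endpoint.

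The synopsis frames the secondary objectives as comparisons, asking whether the two doses "differ in terms of the following events occurring during hospital stay". Section 2.4.2, including its paragraph on 30-day mortality, and the secondary safety endpoint define what is compared. Of the event endpoints the protocol says: "Each of these events will be analysed as a binary outcome and as a time-to-event one". The synopsis adds survival-type summaries, for example that "survival free from need for either non-invasive or invasive mechanical ventilation will be also estimated".

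The endpoints are divided into primary and secondary, for efficacy and for safety. Within the secondary set the protocol gives no testing order, no division of alpha, no adjustment and no statement that the results are exploratory.

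**The concern.** A protocol may leave the handling of secondary multiplicity to the analysis plan. This one goes further and fixes a rule, and the rule covers any result. Read as written, a secondary comparison with p = 0.04 is statistically significant by the protocol's own definition, whatever happened on clinical worsening.

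What is at stake is the claim the trial may make. If the composite is missed, a report could still describe an effect on death, thromboembolism, ventilation or a laboratory marker as statistically significant and cite 4.2 in support. Nothing in the protocol would tell the reader that the error rate across those comparisons was not controlled.

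**Working it through.** **1. The plan's own figure.** Section 2.6 gives the design inputs: "Assuming an alpha of 5% (two tailed"), "clinical worsening in the control group being between 25% and 30"%, and "the study will have 80% power to detect at least 50% relative reduction", with 300 patients allocated 1:1. The usual two-proportion formula per arm is

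n = [z(0.975)·√(2·p̄·(1−p̄)) + z(0.80)·√(p1(1−p1) + p2(1−p2))]² / (p1−p2)².

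For 25% against 12.5%, p̄ = 0.1875, so n = (1.960 × 0.5520 + 0.8416 × 0.5449)² / 0.125² = 2.373 / 0.015625 = 151.9. That is 152 per arm, or 304 in total, close to the stated 300; power with 150 per arm is 79.5%. For 30% against 15% the total is 242, and 300 patients give 87.9% power. The figure reproduces at the lower end of the range. The 5% is used there for one comparison only and implies nothing about the secondary endpoints.

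**2. Count of secondary endpoints.**

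| Group | Endpoints | Number |
| --- | --- | --- |
| In-hospital clinical events (2.4.2) | death; myocardial infarction; thromboembolism; ventilation in patients on standard oxygen; invasive ventilation in patients on non-invasive support | 5 |
| Laboratory (2.4.2) | D-dimer; fibrinogen; mean platelet volume; lymphocyte/neutrophil ratio; IL-6 | 5 |
| Mortality at 30 days | death | 1 |
| Secondary safety | clinically relevant non-major bleeding | 1 |
| **Total** | | **12** |

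The secondary objectives in the synopsis give the same 12. Major bleeding is the primary safety endpoint and is not counted.

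**3. Independent tests.** With no true difference and one two-sided test at 0.05 per endpoint, the chance of at least one p < 0.05 is 1 − 0.95^12 = 1 − 0.540 = 46.0%.

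**4. Correlated tests.** The protocol gives no correlation, so a range is assumed. Take Z_i = √ρ·U + √(1−ρ)·E_i for i = 1 to k, with U and E_i independent standard normal, and count how often max|Z_i| exceeds 1.96. With 400,000 draws the Monte Carlo standard error is at most √(0.25/400,000) = 0.0008.

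| Common correlation ρ | 12 tests | 10 tests |
| --- | --- | --- |
| 0 | 46.0% | 40.2% |
| 0.1 | 45.1% | 39.4% |
| 0.3 | 39.7% | 35.1% |
| 0.5 | 31.9% | 28.6% |
| 0.8 | 18.6% | 17.3% |

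**5. Sensitivity.**

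- *Block structure.* A single correlation across such different endpoints is crude. As an alternative, set the two death endpoints at 0.9, the other clinical events and the markers at 0.2 to 0.6 within their own group, and everything else at 0. The result runs from 43% (at 0.2) to 35% (at 0.6), inside the range in step 4.
- *Sparse events.* Tests on few events are conservative and reject less than 5% of the time. The 10-test column shows the effect if two endpoints contribute nothing.
- *Duplicate analyses.* Two analyses for each of the seven event endpoints and two post-baseline times for each of the five markers make 7×2 + 5×2 = 24 tests. If independent, 1 − 0.95^24 = 70.8%. But a binary and a time-to-event analysis of the same event are nearly the same test. With illustrative within-pair correlations of 0.95 for these and 0.7 for one marker at two times, the chance is about 59% at between-endpoint correlation 0 and about 41% at 0.5.

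**6. The primary comparison.** Its test rejects on its own p-value alone. Adding secondary tests does not change that probability.

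**The case against.** The best case against the point is that it is mostly about something absent. The analysis plan is not at hand, and secondary multiplicity usually belongs there. The sentence in 4.2 is a generic convention sitting beside the interval convention and the software name. It does not claim family-wise control, and it does not say the trial succeeds on a secondary endpoint if the primary fails. The protocol separates primary from secondary endpoints, the sample size rests on the clinical-worsening rate, and parts of the synopsis use the language of estimation.

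Much of this stands. There is a hierarchy between primary and secondary; what is missing is any order or status within the secondary set. The main conclusion is protected. But the reply does not dispose of the sentence itself. It is a stated rule, it applies to any result, and an analysis plan that confined significance to the primary endpoint would be narrowing what the protocol says. The correction therefore belongs in the protocol.

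Three stronger readings are tempting and are not supported:

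- A reader might put the risk at one in three. For 12 tests that needs a common correlation near 0.5, which the documents do not give.
- A reader might say the error is several times the protocol's 5%. The protocol states 5% for a single comparison and as a per-result threshold, never for the secondary family, so the ratio compares unlike things.
- A reader might quote 46% to 71% from 24 tests at common correlation 0.5 to 0. That treats near-duplicate analyses as no more alike than unrelated endpoints. Two separate tests per marker are also assumed, since the synopsis speaks only of variation over three time points.

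**Conclusion.** The point holds as a rule drawn too broadly. Under no true effect, with one test for each of 12 secondary endpoints, the chance of at least one false significant result is about 19% to 46% for an assumed common correlation of 0.8 down to 0. Sparse endpoints pull the figure down and the duplicate analyses push it up, and the documents do not allow a single value within the range.

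The consequence is moderate. A reader might infer that the primary result is compromised; it is not, because its type I error does not depend on the secondary tests. What is affected is the standing of any secondary result reported as significant. The wording should be corrected.

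**What to change.** In section 4.2, replace the general rule with text to this effect:

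*The two-sided 0.05 significance level applies to the primary efficacy comparison only. Secondary efficacy, laboratory and clinically relevant non-major bleeding comparisons are exploratory. They will be reported as estimates with 95% confidence intervals, not adjusted for multiplicity, and without a claim of statistical significance. Major bleeding, the primary safety endpoint, will always be reported with its 95% confidence interval, whatever the efficacy result.*

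The analysis plan should carry the same text. A single gated test of 30-day mortality after a significant primary result is an option, but it is a design choice and not needed to correct the rule. The new text does not settle which analysis of clinical worsening, binary or time-to-event, is decisive, nor how the interim look in section 4.4 bears on the final 0.05 level; both need their own statement.

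The cost is a few sentences, with no added patients, data or procedures. What is given up is the right to call an isolated secondary p-value below 0.05 statistically significant.
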